#### Genetic factors

Individual differences in genetic makeup may play a significant role in shaping the efficacy of neuromodulatory interventions such as tDCS. Genetic factors that influence synaptic plasticity, neurotransmitter function, or vulnerability to neurodegeneration are hypothesized to interact with tDCS-induced neuroplasticity. Although this interaction remains untested in PPA (Wang Z. et al., 2024), related evidence from other neurodegenerative disorders, post-stroke aphasia, and healthy aging provides a compelling theoretical basis for examining genetic predictors in this context.

The brain-derived neurotrophic factor (BDNF) gene plays a central role in regulating synaptic plasticity, neuronal survival, and long-term potentiation and fluctuations in its levels are associated with neuropathological changes observed in neurodegenerative disorders (see Azman and Zakaria, 2022; Ibrahim et al., 2022) for reviews on the molecular mechanism of action). A common single-nucleotide polymorphism, Val66Met (rs6265), is associated with decreased activity-dependent secretion of BDNF (Lamb et al., 2015) which may impair learning and memory; however, this finding is not supported by Bugge Kambestad et al. (2023). Structurally, individuals with the Val66Met gene show smaller hippocampal volume (Molendijk et al., 2012; Hajek et al., 2012; Kambeitz et al., 2012) and cortical thinning in regions relevant to PPA, such as the left frontal and temporal lobes (Yang et al., 2012), potentially impacting their responsiveness to tDCS-based interventions. Functionally, the Val66Met genotype is associated with greater decline in episodic memory and learning impairments (Lim et al., 2021; Cechova et al., 2020; Thomson et al., 2024). In individuals living with post-stroke aphasia, BDNF polymorphism has been linked to aphasia severity and stimulation-induced neuroplasticity (Dresang et al., 2022). In an RCT involving tDCS and language therapy in individuals living with post-stroke aphasia, BDNF val/val carriers showed greater benefit from a-tDCS and aphasia therapy than val/met carriers (Fridriksson et al., 2018). However, this advantage was not observed in a study of aphasia recovery without neuromodulation (de Boer et al., 2017).

The catechol-O-methyltransferase (COMT) gene encodes the COMT enzyme, which plays a crucial role in the degradation of dopamine, particularly in the prefrontal cortex. The Val158Met polymorphism affects enzymatic activity, with Met carriers exhibiting lower COMT activity and thus higher extracellular dopamine levels (Schacht, 2016), which may confer advantages in certain cognitive tasks but can also lead to inefficiencies under high-load conditions. The COMPT effect may be modulated by sex (Elton et al., 2017; Fan et al., 2020). In cognitively unimpaired older adults, COMT Val carriers benefited significantly from tDCS more than those with met/met genes (Hayek et al., 2021).

Finally, the APOE4 allele, particularly in its homozygous form, is a well-established genetic risk factor for Alzheimer's disease (AD), influencing Aβ plaque formation, tau aggregation, and synaptic loss (Sun et al., 2023). It has also been implicated in altered neuroplasticity and cognitive function, even in persons without AD (Corbo et al., 2023; Zimmermann et al., 2019). In the context of PPA, APOE4 is associated with increased β-amyloid deposition and disrupted neural connectivity, contributing to the disease's pathophysiology (Singh et al., 2023). However, its effects are heterogeneous across different phenotypes and subtypes of the disease. Homozygosity is linked to more severe disease progression and potentially poorer treatment response. Moreover, emerging evidence suggests that the APOE4 genotype may influence the effectiveness of tDCS. A recent study by Kang et al. (2021) found that cognitive remediation combined with tDCS slowed decline, with significantly greater benefits observed in APOE4 non-carriers. Understanding the specific pathways affected by APOE4 can guide the development of targeted interventions that may mitigate its adverse effects on PPA progression.

Taken together, BDNF, COMT, and APOE genotypes represent biologically plausible moderators of tDCS efficacy, influencing structural integrity, excitatory-inhibitory balance, and neuroplastic capacity. The present trial is the first to investigate these interactions in PPA and may help identify genetic profiles associated with enhanced responsiveness to neuromodulatory therapies.

#### Blood biomarkers

The role of biomarkers in relation to tDCS outcomes in individuals living with PPA remains largely unexplored, though several markers may offer insight into disease progression and therapy response. Neurofilament light chain (NfL), a neuronal cytoskeletal protein that plays a crucial role in maintaining the structural integrity of axons, is recognized as a valuable biomarker in the context of neurodegenerative disorders. It is released during neuroaxonal damage, making it a sensitive-but-not-specific biomarker for neurodegenerative processes (Matias-Guiu et al., 2019; Steinacker et al., 2017; Lin et al., 2019). The impact of NfL on therapy response in individuals living with PPA, however, remains unknown.

Additionally, tau is a microtubule-associated protein primarily found in neurons, which, when abnormally phosphorylated or fragmented, can aggregate and contribute to the development of neurodegenerative disorders. It can be an important biomarker in PPAs associated with tauopathies (Shir et al., 2024), and its presence in biological fluids may offer insights into disease progression and treatment efficacy, enhancing clinical utility.

Finally, the impact of amyloid-beta 42 (Aβ42) on language therapy efficacy in PPA is complex, encompassing neurodegeneration and therapeutic strategies. In individuals with lvPPA, the presence of Aβ42, signifying Alzheimer's disease, has been found to correlate with increased cortical atrophy, especially in the left hemisphere, and language deterioration, potentially influencing therapy results (Rogalski et al., 2019). This left hemisphere predominant atrophy correlates with a more significant decline in language performance, potentially reducing the efficacy of language therapy (Rogalski et al., 2019). To our knowledge, there has been no research exploring the interaction between Aβ pathology and neural mechanisms to better understand their combined impact on treatment efficacy in PPA. Together, these biomarkers could eventually inform individualized prognoses or treatment decisions; however, their role in moderating or mediating response to tDCS remains an open and important area for future investigation.

#### Lifelong experiences and lifestyle

Similar to genetic factors and biomarkers, lifelong language experiences, such as bilingualism, and lifestyle factors, including exercise and sleep habits, have been argued to influence cognitive reserve and neural plasticity, thereby affecting the efficacy of therapy. For example, bilingual individuals with post-stroke aphasia have been shown to benefit more from therapy and have better recovery than their monolingual peers (Masson-Trottier et al., 2022; Lahiri et al., 2021). However, to our knowledge, bilingualism in individuals living with PPA has not been investigated as a predictor of therapy outcomes (Norhan et al., 2023). Exercise has also proven to maintain and potentially improve cognitive functions in aging (Krivanek et al., 2021) and individuals with post-stroke aphasia (Lorenzen and Murray, 2008). Understanding the interplay between these factors and therapy outcomes could provide valuable insights for optimizing treatment approaches and enhancing clinical care for individuals with PPA.

In summary, studies focusing on behavioral treatment of common symptoms in individuals living with PPA, such as anomia and agraphia, have shown promising results in terms of improvements in trained items immediately following intervention, as well as generalization to untrained items and retention of therapy gains weeks after the intervention ends (Robinaugh and Henry, 2022; Taylor-Rubin et al., 2021; Cadorio et al., 2017; Wauters et al., 2023). Neuromodulation methods, especially tDCS, have further enhanced these outcomes, promoting the maintenance and generalization of language behaviors (Cotelli et al., 2020; Coemans et al., 2021; Nissim et al., 2020). However, a Phase II multisite study has yet to be performed to evaluate large-scale efficacy and further assess safety, examining the benefits of tDCS in individuals with PPA. Furthermore, predicting therapy outcomes in PPA remains complex, influenced by factors such as PPA variant, neuroanatomical and neurofunctional factors, and baseline cognitive abilities. Significant gaps remain in understanding the roles of genetic factors, biomarkers, and lifelong language experiences in shaping therapeutic outcomes, particularly with tDCS. Addressing these gaps is important for optimizing treatment approaches and improving clinical care and neuromodulation outcomes for individuals with PPA.

Despite promising findings from the previous single-site Phase II study using tDCS paired with similar language therapy in PPA (Tsapkini et al., 2018) and other studies from members of our group (Roncero et al., 2017, 2019; Hung et al., 2017; Nissim et al., 2022; McConathey et al., 2017), no multisite Phase II trial has systematically evaluated its efficacy, which is a helpful step to facilitate transfer of tDCS into the clinical environment. This gap is significant given the encouraging learning and generalization effects observed in lvPPA and nfvPPA populations. The present study is designed to address this gap by evaluating the impact of combined tDCS and behavioral therapy on naming and spelling in a well-powered multisite randomized controlled trial (RCT), and by identifying clinical, neural, and genetic predictors of treatment response. A crossover RCT enables each participant to serve as their own control, increasing power and reducing inter-individual variability.

### Objectives

This paper reports the protocol and analysis plan for the clinical trial NCT05386394, registered on http://clinicaltrials.gov, which implements a multisite, randomized, double-blind, sham-controlled, within-subject crossover design. The trial aims to assess the effectiveness of a-tDCS targeting the left IFG combined with a novel, theoretically driven behavioral naming treatment in improving spoken naming and spelling abilities in individuals with lvPPA or nfvPPA. The overall goal is to bring tDCS combined with spoken naming and spelling therapy from the research lab closer to the clinic. We hypothesize that a-tDCS targeting the left IFG concurrent with spoken naming and spelling therapy will yield superior improvements compared to sham-tDCS (s-tDCS) paired with the same behavioral therapy, with sustained effects for up to 3 months post-treatment and generalization to untrained items as well as broader language and cognitive tasks subserved by the same area of stimulation. Additionally, we aim to evaluate factors already identified as potential predictors of treatment response, including PPA subtype, aphasia severity, cortical and neurofunctional measures, cognitive abilities, genetic markers, lifelong language experience, and demographic variables such as age and sex.

## Methods and analysis

Table 1 provides the Standard Protocol Items: Recommendations for Interventional Trials (SPIRIT) details for the clinical trial regarding enrollment, interventions, and assessments (Chan et al., 2013).

**Table 1 T1:**
[figure not shown]
Standard Protocol Items: Recommendations for Interventional Trials (SPIRIT) details for the schedule of enrollment, interventions, and assessments, summarized version.

See Supplementary material for the detailed version of this table.

Interventions: NaSp, Naming and Spelling therapy; a-tDCS, active-transcranial direct current stimulation; s-tDCS, sham-transcranial direct current stimulation.

Assessments: Behavior-Comportment-Personality and Language Domains of the Frontotemporal Lobar Degeneration-Modified Clinical Dementia Rating (FTLD-CDR) (Knopman et al., 2008), Clinical Dementia Rating Scale (CDR) (Morris, 1993), Montreal Cognitive Assessment (MoCA) (Nasreddine et al., 2005).

### Trial design and settings

Building on a previous trial led by members of our team (NCT02606422), this study will employ a randomized, double-blind, sham-controlled, within-subject crossover design. Participants will be randomly assigned to one of two crossover groups (see Figure 1 for a visual representation of the timeline). Group 1 will receive a-tDCS over the left IFG, combined with Naming and Spelling therapy (NaSp), during Intervention Period 1, and s-tDCS over the left IFG, combined with NaSp, during Intervention Period 2. Conversely, Group 2 will receive NaSp with s-tDCS over the left IFG during intervention Period 1 and NaSp with a-tDCS over the left IFG during intervention Period 2.

**Figure 1 F1:**
[figure not shown]
Time course of the study (15 NaSp intervention sessions per period) and evaluations for each group of participants in the crossover design. Beh ass, behavioral assessment; Bio, Biomolecular data; MRI, MRI scan; NaSp, Naming ans Spelling therapy; a-tDCS, active-transcranial direct current stimulation; s-tDCS, sham-transcranial direct current stimulation.

Participants will be recruited through referrals from their neurologist, FTD, or AD research centers at each university, self-referrals via clinicaltrials.org, and in-house participant banks. This multi-site study is conducted across four research settings: Johns Hopkins School of Medicine, University of Pennsylvania, Baycrest Academy of Health Sciences and Geriatric Research, and Lady Davis Research Institute. All assessments and therapy sessions will be in person at the research facility. Participants will not receive these interventions in their clinical care context.

### Data collection

Demographic characteristics will be collected at the enrollment session (T0) after obtaining informed consent and the eligibility screening. Medical records will also be collected at that point. Saliva samples will be collected at baseline (T1) and blood samples will be collected before P1 (T1), at 3 months after P1 [i.e., before P2 (T4)], and at 3 months after P2 (T7).

Each participant will undergo clinical, cognitive, and language assessments at seven time points throughout the study: before intervention period 1 (P1) (T1), after P1 (T2), 4 weeks after P1 (T3), and 3-month after P1 [T4, also serving as before intervention period 2 (P2)], after P2 (T5), 8 weeks after P2 (T6), and at 3-month after P2 (T7). Figure 1 provides an overview of the study time course. Primary and secondary outcome measures will be consistently assessed for each participant, and the assessor will remain blinded to the participant's treatment allocation throughout all visits. Surrogate outcomes [Magnetic Resonance Imaging (MRI) scans] will be obtained before P1 (T1), at 3 months after P1 [i.e., before P2 (T4)], and at 3 months after P2 (T7).

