## Abstract

Primary progressive aphasia (PPA) is a neurological syndrome characterized by the gradual deterioration of language capabilities. Due to its neurodegenerative nature, PPA is marked by a continuous decline, necessitating ongoing and adaptive therapeutic interventions. Recent studies have demonstrated that behavioral therapies, particularly when combined with neuromodulation techniques such as transcranial direct current stimulation (tDCS), can improve treatment outcomes, including the long-term maintenance and generalization of therapeutic effects. However, there has yet to be a phase II multisite study examining the efficacy of tDCS in individuals with PPA. This paper reports the methods and analyses for the clinical trial NCT05386394. A total of 120 adults with non-fluent and logopenic variant PPA will receive a novel spoken Naming and Spelling (NaSp), individuals with semantic variant PPA will be excluded from this trial. Participants will receive NASP therapy over two periods of 3 weeks (Monday through Friday, for a total of 15 non-consecutive days) combined with anodal (a-tDCS) and sham tDCS (s-tDCS). They will be randomly allocated to receive a-tDCS either during the first or second intervention period. The study will be conducted at four sites across the United States and Canada. Outcome measures will be recorded immediately before and after each intervention period, as well as 3 months after each period. Primary outcome measures will be the change in phonemic accuracy in spoken picture naming and letter accuracy in spelling for trained nouns and verbs. Changes from the a-tDCS and s-tDCS periods will be compared to determine the efficacy of tDCS. Primary outcomes will be analyzed using statistical methods that account for repeated measures within participants (namely generalized estimating equations). A significant adjuvant effect of tDCS will be determined if differences in phonemic accuracy and/or letter accuracy immediately following a-tDCS intervention and/or at the 3-month follow-up are greater (at p < 0.05) than those of the s-tDCS intervention. This trial is the first multisite, fully powered, randomized, double-blind, sham-controlled, crossover study of the effectiveness of tDCS as an adjuvant to behavioral treatment for spoken naming and spelling deficits in individuals with PPA. Specific challenges in designing the protocol are considered.

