### Statistical analysis

This trial investigates whether combining tDCS targeting the left IFG with a tailored spoken naming and spelling therapy improves language abilities and communication in individuals with PPA, with expected benefits extending to untrained tasks and lasting up to 3 months. It also aims to identify predictors of treatment response.

The primary outcomes will be analyzed using a general crossover formulation that considers each follow-up time point, the effects of treatment (s-tDCS vs. a-tDCS), phase (P1 or P2), and their interaction. For each participant, the data will include the order of treatments (s-tDCS in phase 1 and a-tDCS in phase 2, or vice versa) and changes in accuracy from before to after each phase for phonemic accuracy (during spoken naming) and letter accuracy (during spelling) of trained items.

The general crossover analysis will estimate parameters such as intervention effects in each phase and the overall average intervention effect. Estimates of these effects, standard errors, and confidence intervals will be calculated using the generalized estimating equation (GEE) method with robust variance estimation to account for correlations among repeated outcomes across different time points and phases within an individual. *P*-values will be exact and derived by comparing the estimates to the distribution calculated by permuting the order of intervention assignment across patients.

To address potential carryover effects inherent in the within-subject crossover design, a period-by-treatment interaction term will be included in the GEE model. A significant interaction will indicate possible carryover. In this case, follow-up sensitivity analyses will be conducted such as restricting analyses to Period 1 only, to confirm whether the treatment effect is robust. Washout adequacy will also be examined based on baseline performance at each phase.

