## Discussion

The treatment of language difficulties in PPA remains a significant challenge and a high-priority, unmet medical need. Addressing this complex issue requires a transformative approach. Recent advances in communication disorder treatments for PPA have largely come from non-invasive neuromodulation techniques, such as tDCS. This RCT stands to be the first multisite Phase II study evaluating tDCS's efficacy as an adjuvant for behavioral interventions in PPA therapy, representing a critical step toward addressing this need.

This trial employs a randomized, double-blind, sham-controlled, within-subject crossover design, with follow-ups conducted immediately after therapy and at 4 weeks and 3 months post-therapy. It evaluates the effectiveness of tDCS administered over left perisylvian language areas, combined with a novel, cognitive model-driven behavioral therapy called NaSp. Together, these interventions aim to enhance spoken naming and spelling abilities and ultimately communication in individuals living with lvPPA and nfvPPA. Intending to replicate and validate prior findings, this study seeks to advance evidence on combining neuromodulation techniques with established language interventions.

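### The middle follow-up is set at 4 weeks after Period 1 but 8 weeks after Period 2, against a single 4 weeks in the Discussion; if real, the mismatch confounds phase with time since therapy at that visit

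*Protocol article*

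**What the plan says.** The Data collection section lists seven assessments. After Period 1 they fall "after P1 (T2), 4 weeks after P1 (T3), and 3-month after P1" (T4, which also serves as the baseline for Period 2). After Period 2 they fall "after P2 (T5), 8 weeks after P2 (T6), and at 3-month after P2 (T7"). T3 and T6 are the matching middle visits, at 4 and 8 weeks, and no reason is given for the difference.

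The Discussion describes one schedule for the whole trial, "with follow-ups conducted immediately after therapy and at 4 weeks and 3 months post-therapy". The Abstract does not name a middle visit: "Outcome measures will be recorded immediately before and after each intervention period, as well as 3 months after each period".

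The Statistical analysis section analyses the primary outcomes with a "general crossover formulation that considers each follow-up time point, the effects of treatment (s-tDCS vs. a-tDCS), phase (P1 or P2), and their interaction". It then says of the period-by-treatment term: "A significant interaction will indicate possible carryover". In that event, sensitivity analyses follow, for example "restricting analyses to Period 1 only, to confirm whether the treatment effect is robust". Nothing in this section exempts T3 and T6.

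**The concern.** Data collection and the Discussion cannot both be right about Period 2. If the 8 weeks is a slip, the text needs correcting. If it is the real schedule, it matters for the analysis.

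A crossover comparison at a given visit assumes that the two periods are observed at the same time after treatment. Under the unequal schedule, phase and time since therapy are the same variable at the middle visit. Randomising the order does not help, because both sequences follow the same calendar. Two things follow at that visit. The treatment effect belongs neither to week 4 nor to week 8. The interaction also picks up any fading of the tDCS benefit between those weeks, and the plan would label that possible carryover.

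**Working it through.** **Does the stated trial length settle the conflict?** The Outcome measures section gives seven assessments over 33 weeks. Two 3-week therapy periods and two 12-week follow-ups make 3 + 12 + 3 + 12 = 30 weeks; adding three assessment weeks gives 33. T6 lies inside the last 12 weeks whether it is at week 4 or week 8, so the total fits both. The document gives no figure for the middle-visit effect or the interaction, so there is none to reproduce.

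**Expectations with no carryover.** Let d(t) be the active-minus-sham effect t weeks after therapy, and let m₁ and m₂ be the sham-level changes at the middle visit of Periods 1 and 2.

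| Sequence | Period 1 (week 4) | Period 2 (week 8) |
|---|---|---|
| Active then sham | m₁ + d(4) | m₂ |
| Sham then active | m₁ | m₂ + d(8) |

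- Phase-adjusted treatment effect: half the difference between sequences in (Period 1 − Period 2) = [d(4) + d(8)]/2.
- Period-by-treatment interaction: the difference between sequences in (Period 1 + Period 2) = d(4) − d(8).

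The terms m₁ and m₂ cancel, so general decline biases neither quantity. With the same interval after both periods the interaction is zero.

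**Size as a share of the initial effect.** The document gives no course over time, so the shapes below are assumptions (linear change, 3 months taken as 13 weeks).

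| Benefit at week 13 | d(4) | d(8) | Average | Interaction |
|---|---|---|---|---|
| Fully sustained | 1 | 1 | 1 | 0 |
| Half | 1 − 0.5 × 4/13 = 0.846 | 1 − 0.5 × 8/13 = 0.692 | 0.769 | 0.154 |
| Zero | 1 − 4/13 = 0.692 | 1 − 8/13 = 0.385 | 0.538 | 0.308 |

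If the interaction were pooled equally over the three follow-up visits, with the other two contributing nothing, 0.154 becomes 0.154/3 = 0.051 and 0.308 becomes 0.103.

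**How often this would look like carryover.** Assumptions: a 15-point advantage at the end of therapy (the Introduction reports over 15% more improvement in the team's spelling trials), exponential decay to a stated fraction at week 12, standard deviation of change 10 to 20 points, within-person correlation 0.5, and n = 120 × 0.85 = 102. The standard error of the interaction is √[2·SD²·(1 + 0.5)·(2/51)]. At SD 15 this is √(675 × 0.0392) ≈ 5.1 points.

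| Retained at week 12 | d(4) | d(8) | Interaction (points) | Significant at nominal 5% (SD 20 to SD 10) |
|---|---|---|---|---|
| 100% | 15.00 | 15.00 | 0 | 5% |
| 75% | 13.63 | 12.38 | 1.25 | 5.4% to 6.5% |
| 50% | 11.91 | 9.45 | 2.46 | 6.5% to 11% |
| 25% | 9.45 | 5.95 | 3.50 | 8% to 17.5% |

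These rates are for the middle visit tested alone. A simulation (4,000 trials, 51 per sequence, 50% retention, SD 15) agrees. Visits at 4 and 8 weeks gave a mean interaction of 2.37 points, an average effect of 10.65 and 7.6% rejections. Visits at 4 and 4 weeks gave −0.03 points, 11.92 and 4.5%.

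**The case against.** Several points on the other side are sound and limit this one.

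- **The success criterion.** A reader might infer that the trial's main claim is compromised. The documents do not support that. The Abstract rests success on the difference immediately after the intervention and/or at 3 months. T2/T5 and T4/T7 are at equal intervals after their periods, so those visit-specific contrasts are intact.
- **A sustained benefit.** The Objectives hypothesise effects lasting up to 3 months. If that holds between weeks 4 and 8, the false interaction is zero. Decay to zero by week 13 is an extreme case that contradicts the hypothesis.
- **A possible slip.** The Discussion points to one interval, and Figure 1, Table 1 and the supplementary schedule are not available here. The text conflicts for certain; it is not certain that participants are seen at unequal times.
- **The consequence of a false signal.** A significant interaction leads to sensitivity analyses and does not replace the primary analysis. Washout is also examined from the baselines of each phase. The document does not say whether the interaction is fitted by visit or pooled; by visit, the checks at the aligned visits are untouched.
- **Within-participant comparison.** A reader might infer that it is lost at the middle visit. It is not: each participant still contributes an active and a sham value, and the phase term absorbs common decline. What changes is the quantity estimated.

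These points do not remove the contradiction. Nor do they remove the confounding at T3/T6 if the schedule is followed as written. The maintenance of the benefit is something the trial sets out to measure, so the analysis should not depend on it.

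**Conclusion.** The concern stands in a limited form. That Data collection and the Discussion disagree on the middle visit is certain. The statistical consequence depends on two conditions: that the unequal schedule is real, and that the tDCS benefit changes between weeks 4 and 8.

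If both hold, the middle-visit interaction is d(4) − d(8) without any carryover. That is about 15% of the initial effect under linear decline to half by week 13, and about 5% if pooled equally over three visits. Under the assumed variances, false carryover signals at this visit rise only modestly above 5% when at least half the benefit is retained. The misreading would affect the interpretation of carryover and of the middle-visit effect. The immediate and 3-month contrasts are unaffected.

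**What to change.** Reconcile Data collection and the Discussion so that the middle visit falls at the same interval after both periods. The sponsor decides which interval, and Figure 1, Table 1 and the supplementary schedule should be checked against it.

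If any participants were seen at unequal intervals, base the period-by-treatment (carryover) test on the aligned visits only (T2/T5 and T4/T7), and report T3 and T6 by actual weeks since the end of therapy.

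The cost is a text correction or a small amendment, with no added visits. Where the second step applies, the carryover test uses slightly less data.
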